## Abstract

**Introduction:**

Mortality among children hospitalised for complicated severe acute malnutrition (SAM) remains high despite the implementation of WHO guidelines, particularly in settings of high HIV prevalence. Children continue to be at high risk of morbidity, mortality and relapse after discharge from hospital although long-term outcomes are not well documented. Better understanding the pathogenesis of SAM and the factors associated with poor outcomes may inform new therapeutic interventions.

**Methods and analysis:**

The Health Outcomes, Pathogenesis and Epidemiology of Severe Acute Malnutrition (HOPE-SAM) study is a longitudinal observational cohort that aims to evaluate the short-term and long-term clinical outcomes of HIV-positive and HIV-negative children with complicated SAM, and to identify the risk factors at admission and discharge from hospital that independently predict poor outcomes. Children aged 0–59 months hospitalised for SAM are being enrolled at three tertiary hospitals in Harare, Zimbabwe and Lusaka, Zambia. Longitudinal mortality, morbidity and nutritional data are being collected at admission, discharge and for 48 weeks post discharge. Nested laboratory substudies are exploring the role of enteropathy, gut microbiota, metabolomics and cellular immune function in the pathogenesis of SAM using stool, urine and blood collected from participants and from well-nourished controls.

**Ethics and dissemination:**

The study is approved by the local and international institutional review boards in the participating countries (the Joint Research Ethics Committee of the University of Zimbabwe, Medical Research Council of Zimbabwe and University of Zambia Biomedical Research Ethics Committee) and the study sponsor (Queen Mary University of London). Caregivers provide written informed consent for each participant. Findings will be disseminated through peer-reviewed journals, conference presentations and to caregivers at face-to-face meetings.

Strengths and limitations of this studyRigorous collection of longitudinal data on morbidity, mortality and nutritional status during inpatient care and for 48 weeks after initial admission for severe acute malnutrition (SAM) in HIV-positive and HIV-negative children.Laboratory substudies investigating enteropathy, microbiota, metabolomics and immune cell function provide a unique opportunity to understand which pathogenic pathways contribute to SAM and whether these processes normalise with nutritional rehabilitation.High loss to follow-up due to participants returning to home settings following hospital discharge.The clinical heterogeneity of the study participants, including comorbidities such as infections, may make it challenging to identify the specific causes of clinical outcomes.Potential bias in recruiting well-nourished controls only from hospitals will be reduced by inclusion of community-based controls, including well-nourished siblings of children with SAM.

## Introduction

Malnutrition underlies almost half of all childhood deaths in developing countries.^1^ Severe acute malnutrition (SAM) is defined by a weight-for-height Z-score (WHZ) <–3, mid-upper arm circumference (MUAC) <115 mm and/or bilateral pitting oedema.^2^ Current treatment guidelines distinguish two groups: (i) children with uncomplicated SAM who can be managed in the community and (ii) children with complicated SAM, who are hospitalised and undergo resuscitation, stabilisation and nutritional rehabilitation. In-hospital mortality in children with complicated SAM remains high despite the implementation of WHO guidelines.^3^ Furthermore, SAM presents as two major clinical phenotypes: non-oedematous SAM (marasmus), characterised by severe wasting, and oedematous SAM (kwashiorkor), a more complex syndrome characterised by bilateral pitting oedema, steatosis and diarrhoea.^4 5^ Despite differing clinical outcomes, treatment protocols are the same for both oedematous and non-oedematous SAM.

A contributory factor to high inpatient mortality is the co-occurrence of HIV infection in around one-third of children hospitalised for SAM in sub-Saharan Africa.^6 7^ While new HIV infections in children have declined,^8^ a substantial number of infected children are diagnosed late and present with malnutrition. There is also a growing population of HIV-exposed uninfected (HEU) children who have immune abnormalities, poor growth and higher risk of mortality and infectious morbidity.^9^ Hence, HIV has transformed the epidemiology and outcomes of SAM.^10^ Even with standardised treatment approaches, inpatient deaths are almost fourfold higher among HIV-positive children with SAM (herein termed HIV-SAM) compared with HIV-negative children with SAM (30.4% vs 8.4%), for reasons that remain unclear^10^; this mortality is threefold higher than would be expected from anthropometric parameters alone.^10^ Management of HIV-SAM is particularly challenging because HIV fundamentally alters the clinical presentation of malnutrition and the response to treatment. Children with HIV-SAM are more stunted and wasted; have a higher frequency of persistent diarrhoea; tend to have delayed nutritional recovery and have a more complicated clinical course than HIV-negative children with SAM.^10^

### Long-term outcomes of SAM

Following resolution of complications and return of appetite, children are discharged from hospital to continue therapeutic feeds at home. However, emerging data indicate high post discharge mortality following in-hospital management of SAM.^11–13^ Malnutrition, together with young age, HIV infection and pneumonia, has been associated with higher post discharge mortality.^14^ One of the largest prospective studies of growth and mortality in children with SAM (FuSAM), conducted in Malawi from July 2006 to March 2007, collected 12-month outcome data on 87% of 1024 children admitted to the nutrition ward.^11^ A total of 427 (42%) died and 44% of these deaths occurred after discharge from hospital. Survival was greatest among those who were nutritionally cured on discharge from outpatient therapeutic feeding centres, defined as two consecutive visits with >80% expected weight-for-height, no oedema and clinically stable. The risk of mortality after hospital discharge was fourfold higher for HIV-SAM compared with HIV-negative children with SAM, but the outcomes among HEU children were not reported. The loss to follow-up was high in the FuSAM study because there was only one follow-up visit, 1 year after discharge from outpatient-feeding centres. A recent study from Kenya identified malnutrition and HIV infection as key drivers for post discharge mortality, with 52% of deaths attributable to MUAC <11.5 cm and 11% to HIV infection.^15^

The impact of SAM appears to persist beyond the first year after discharge from hospital. The ChroSAM study, which followed children with SAM 7 years post discharge, showed that children had poorer growth, body composition and physical function compared with siblings and community controls, which are all indicators of future cardiovascular and metabolic disease.^12^

While anthropometry is used to assess nutritional recovery after discharge from hospital, the pattern and quality of growth recovery following SAM is poorly understood. The observation that children treated for SAM have a deficit in lean tissue despite regaining weight suggests that assessing body composition in addition to anthropometry may help to identify children who have not completely recovered and are at potential risk of long-term metabolic diseases.^12^ Children with HIV-SAM appear to have potential for catch-up growth in weight-for-age and/or weight-for-height, which have been shown to normalise with treatment even prior to widespread availability of Antiretroviral Therapy (ART)^16^; by contrast, height-for-age shows less potential for catch-up growth.^17^ However, the body composition of children with HIV-SAM compared with HIV-negative children with SAM has not been described. Whether children recover fat mass at the expense of lean mass is unknown, but differences in tissue accretion patterns may have implications for survival and long-term metabolic health.^18 19^ There is also a need to consider the effect of SAM on the size of body parts which grow at different rates: relatively shorter legs, for example, are associated with epidemiological risk of overweight, coronary artery disease, liver dysfunction and diabetes.^20 21^

Taken together, there is clearly an elevated risk of mortality among HIV-positive children with SAM compared with HIV-negative children with SAM, and an ongoing mortality risk among all children with SAM that persists after discharge from hospital. There are several gaps in our understanding of the long-term outcomes: (i) causes of death have not been clearly defined, (ii) no studies have systematically and longitudinally collected morbidity and mortality data or documented repeat hospitalisations post discharge and (iii) the long-term outcomes of HIV-positive children with SAM in the era of ART availability are unclear.

### Pathogenesis of SAM

Better understanding the pathogenesis of SAM may help to explain the high mortality of children both during and after hospitalisation and identify new targets for interventions to supplement existing treatment strategies. Consistent evidence that immune mediators are altered in malnutrition^22^ and that systemic and intestinal inflammation are associated with poor outcomes in SAM^23^ suggests that immune dysfunction contributes to infectious susceptibility.^24^ Malnutrition is also characterised by a complex derangement in gut microbial,^25^ metabolic,^26^ immune^27^ and hormonal pathways, organ dysfunction and micronutrient deficiencies in the context of co-infections, enteropathy and chronic inflammation. Several studies have recently provided insights into these perturbations using new tools,^25 26 28 29^ including metabolomics and metagenomics, but we still lack a clear understanding of many of the pathogenic pathways driving malnutrition, the interactions between these pathways and which are the most tractable targets for intervention.

SAM shares several pathological and clinical features with HIV, which may explain clinical outcomes in these co-occurring conditions: (i) both are characterised by intestinal damage, leading to impairment of the mucosal barrier and increased intestinal permeability; (ii) both have underlying systemic immune activation; and (iii) both are frequently complicated by persistent diarrhoea, pneumonia and sepsis that may plausibly arise due to loss of intestinal barrier function.^30^ Understanding the overlapping impact of HIV and SAM is critical to inform additional interventions to improve outcomes of children with HIV-SAM.

## Objectives of HOPE-SAM

The Health Outcomes, Pathogenesis and Epidemiology of Severe Acute Malnutrition (HOPE-SAM) study has two primary objectives:To describe the short-term and long-term clinical outcomes of children with complicated SAM, with and without HIV infection, and to identify the risk factors at admission and discharge from hospital that independently predict these outcomes.To better characterise the pathogenesis of SAM through nested laboratory substudies evaluating enteropathy, gut microbiota, metabolomics and immune cell function.

## Study design

HOPE-SAM is a longitudinal observational cohort study, enrolling between 600–800 children aged 0–59 months admitted with complicated SAM to the tertiary paediatric wards at two sites in Zimbabwe (Parirenyatwa Hospital and Harare Children’s Hospital) and one in Zambia (University Teaching Hospital, Lusaka). Both HIV-positive and HIV-negative children will be enrolled. Throughout this paper, ‘SAM’ refers to all children, regardless of HIV status; where analyses specifically compare children by HIV status, groups are identified as HIV-positive children with SAM (HIV-SAM) and HIV-negative children with SAM. All participants with SAM are followed for 48 weeks post discharge, with longitudinal data collection and blood sampling. The study contains four nested substudies as shown in figure 1. A subgroup of children will be recruited to the enteropathy substudy for which they will have the same follow-up procedures but more intensive biological specimen collection including stool (all time points), urine after lactulose-mannitol (LM) challenge as an assessment of intestinal permeability and nasogastric aspirate (baseline only); these children are also included in microbiota and metabolomics substudies. Children with SAM for whom blood samples are available are included in the immunology substudy, for which circulating inflammatory mediators will be assayed; functional cellular immunology assays will be conducted for all children in the immunology substudy with sufficient sample volume (>2 mL) recruited after June 2017. A group of healthy children recruited from the same hospitals and communities, who are well-nourished and matched to children in the enteropathy substudy by age and HIV status, will have data and specimens collected to provide normative data for the laboratory substudies; these well-nourished controls will not be followed longitudinally.

**Figure 1 F1:**
[figure not shown]
Study flow chart. All hospital admissions are screened for eligibility for the observational cohort and enteropathy substudy, with procedures undertaken as shown in the flow chart during hospitalisation and post discharge. Well-nourished children from outpatient clinics and the community meeting eligibility criteria as well-nourished controls are enrolled and undergo a single baseline assessment as shown. The immunology, microbiota and metabolomics substudies enrol children as shown. All children with severe acute malnutrition (SAM), regardless of which arm of the study they are enrolled into, are followed for 48 weeks post discharge. ^1^The immunology substudy started from 1 June 2017 and required children to have a blood sample >2 mL to conduct cellular assays. LM, lactulose-mannitol; WHZ, weight-for-height Z-score.

The study protocol, data collection forms and standard operating procedures are available online at https://osf.io/29uaw/.

## Recruitment

### Screening

Caregivers of all hospitalised children are sensitised about the study. All new admissions aged 0–59 months are screened for SAM, which is defined according to WHO criteria as any of WHZ <–3, MUAC <115 mm (if aged 6–59 months) and/or bilateral pitting oedema. All children with SAM are recruited from hospital, and this study therefore focuses on complicated SAM; children with uncomplicated SAM will not be enrolled.

### Eligibility for observational cohort

All children with SAM whose caregivers are willing to provide written informed consent and to learn their child’s HIV status are offered enrolment. Any children who die prior to study enrolment and those with a known malignancy are ineligible.

### Eligibility for enteropathy substudy

Children with SAM aged 6–59 months with a nasogastric tube in place (or due to be placed) are categorised into four groups (HIV-positive oedematous (group A -I); HIV-positive non-oedematous (group A-II); HIV-negative oedematous (group C-I) and HIV-negative non-oedematous (group C-II)) as shown in table 1. Children meeting eligibility criteria will be enrolled throughout the study recruitment period until sufficient specimens have been collected from the groups shown in table 1. Children in the enteropathy substudy are stratified into age bands (6–11 months, 12–23 months and 24–59 months) to enable age-matching of well-nourished controls. Children with underlying chronic gastrointestinal disease or a known malignancy are ineligible.

**Table 1 T1:** Enteropathy substudy groups

Children aged 6–59 months	SAM*		Well-nourished controls WHZ>–1
	Oedematous†	Non-oedematous	
HIV-positive (HIV PCR+ if <18 months; HIV antibody+ if >18 months)	n=50 (group A-I)	n=50 (group A-II)	n=100 (group B)
HIV-negative (HIV PCR– if<18 months; HIV antibody – if>18 months)	n=50 (group C-I)	n=50 (group C-II)	n=100 (group D)

Note that children below 6 months of age are excluded from the enteropathy substudy to avoid interrupting exclusive breast feeding during the lactulose-mannitol test.

*SAM defined according to WHO criteria.

†Presence of bilateral pitting pedal oedema.

SAM, severe acute malnutrition; WHZ, weight-for-height Z-score.

### Eligibility for microbiota and metabolomics substudies

Children enrolled into the enteropathy substudy are also included in the microbiota and metabolomics substudies since these substudies use the stool, urine and plasma samples collected for enteropathy analyses.

### Eligibility for immunology substudy

The immunology substudy comprises all children with SAM (drawn from both the observational cohort and the enteropathy substudy, as shown in figure 1) providing a blood sample of sufficient volume (>2 mL) for cellular assays after 1 June 2017.

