### Well-nourished controls

Controls are children drawn from the same hospitals and communities as cases with SAM (including well-nourished sibling controls), who are aged 6–59 months (matched to enteropathy substudy children within age bands), well-nourished (WHZ >–1) and clinically well (no acute illness or current infections) with known HIV status. Controls are categorised into two groups: well-nourished HIV-positive (group B) and well-nourished HIV-negative (group D), as shown in table 1. Children with underlying chronic gastrointestinal disease or a known malignancy are ineligible. Well-nourished controls provide comparison biomarker data for all the laboratory substudies.

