### Baseline procedures

Baseline data on maternal and household characteristics, the child’s medical history and current illness are collected by a study nurse. Anthropometry, including body composition measured by whole-body (wrist-ankle) bio-electrical impedance analysis (BodyStat 1500MD; BodyStat, UK), leg length using an electronic knemometer (Zimbabwe only, due to availability of knemometers) and triceps, subscapular and supra-iliac skinfold thickness using callipers (Holtain, Crymych, UK), are undertaken at baseline. Blood (1 mL/kg up to 5.4 mL maximum) is collected at baseline into an endotoxin-free EDTA tube for all children and, in the enteropathy substudy, additionally into a PAXgene tube (PreAnalytiX, Hombrechtikon, Switzerland) for subsequent transcriptomic analysis. Blood is not collected from children with severe anaemia (known haemoglobin <60 g/L). HIV testing is carried out in accordance with national guidelines as part of routine clinical practice; where it has not been done, the child’s HIV status is ascertained using a rapid test antibody algorithm for children over 18 months, or HIV DNA PCR for children under 18 months. CD4 count/percentage and viral load are measured in HIV-positive children. Maternal HIV status is documented where available, so that HIV-exposed uninfected children can be identified. Blood samples are sent to research laboratories at each site to conduct whole blood stimulation and bacterial binding assays (as described in the immunology substudy) and to store aliquots of whole blood, peripheral blood cells and plasma at −80⁰C.^31^ In the enteropathy substudy, nasogastric aspirate, stool and urine (after an oral dose of lactulose and mannitol) are also collected. Lactulose and mannitol are ingested by the child after fasting and urine is collected over a 2-hour period to measure recovery of lactulose and mannitol, a measure of intestinal absorptive capacity and permeability, as previously described.^32^

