### Immunology substudy

Integrated profiles of innate immune cell function will be generated for each child using principal components analysis followed by hierarchical clustering.^65 66^ This data -reduction method identifies whether absolute levels of specific markers or relative differences between markers differentiate children into groups. The resulting innate immune profiles will be compared between HIV-SAM, HIV-negative children with SAM and well-nourished groups using univariable tests and multivariable analysis of variance of the principal components.

To address the relationship between immune function and infections, regression analyses will determine whether baseline innate immune profiles (or the individual parameters defining them) are associated with the infectious morbidity or mortality during hospitalisation, using logistic models for binary outcomes and linear models for duration. Key clinical characteristics, including age, sex, oedema and baseline WHZ, will be added to models to investigate their confounding effects. Multivariable stacked regression methods will be used to compare the impact of different factors on severe bacterial infections based on heterogeneity tests.

To determine whether treatment for SAM restores innate immune cell antibacterial function, mixed effects regression models will compare longitudinal changes in individual immune parameters, and the principal components calculated from the weights identified at baseline (which include well-nourished controls). Similarities and differences in longitudinal immune profiles will be compared between groups using non-metric multidimensional scaling.^65 67 68^ This approach will group children according to their composite innate immune function, allowing the duration and variability of immune restoration to be evaluated over the course of nutritional rehabilitation. Binary logistic regression will determine whether innate immune profiles at discharge are associated with morbidity or mortality during follow-up.

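### SAM infants under 6 months enter the immunology substudy but have no control of their age, so any age difference in innate function would be confounded with SAM

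*Protocol article*

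**What the plan says.** All references are to the protocol article.

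- **Cases.** Study design describes "enrolling between 600–800 children aged 0–59 months admitted with complicated SAM", and Screening repeats the range: "All new admissions aged 0–59 months are screened for SAM". Under Eligibility for immunology substudy the cases are "all children with SAM (drawn from both the observational cohort and the enteropathy substudy, as shown in figure 1"). The only further limits are "providing a blood sample of sufficient volume (>2 mL) for cellular assays after 1 June 2017". No lower age limit is given.
- **Controls.** The section Well-nourished controls sets their age at 6–59 months, "matched to enteropathy substudy children within age bands". It then assigns them to every substudy: "Well-nourished controls provide comparison biomarker data for all the laboratory substudies".
- **Reason for the 6-month floor.** The note to Table 1 excludes younger infants from the enteropathy substudy so that the lactulose-mannitol test does not interrupt exclusive breast feeding. No corresponding reason is given for immunology.
- **Analysis.** Analysis, Immunology substudy, states: "The resulting innate immune profiles will be compared between HIV-SAM, HIV-negative children with SAM and well-nourished groups using univariable tests", together with multivariable analysis of variance of the principal components. Age is named in the next paragraph, for the models relating immune profiles to infection. Component weights found at baseline, with controls included, are carried into the longitudinal models.

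**The concern.** Eligibility, control selection and comparison method are each stated, and for immunology they do not fit together. The microbiota and metabolomics substudies use the enteropathy children, so the same controls suit them. Immunology alone draws cases from outside the matched set, including an age stratum with no controls at all.

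The substudy's first hypothesis is that SAM compromises the antibacterial function of innate cells. A SAM-versus-control difference is the direct evidence for it. If innate function in the first six months differs from that at 6–59 months, part of that difference would reflect age. The same would apply to the component weights, which are derived on the combined baseline set.

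An age covariate cannot repair the youngest stratum. With no control under 6 months, adjustment there is extrapolation from older children.

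**Working it through.** **1. Does the blood-volume rule act as an age floor?** Baseline procedures gives the draw: "Blood (1 mL/kg up to 5.4 mL maximum) is collected at baseline". More than 2 mL therefore needs a weight above 2 mL ÷ 1 mL/kg = 2 kg. That is an arithmetic minimum. The volume rule, and the rule against bleeding children with known haemoglobin below 60 g/L, may thin out the smallest infants but do not exclude the under-6-month group.

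**2. Cases and controls by age.**

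| Age at baseline | SAM cases eligible | Controls |
|---|---|---|
| 0–5 months | yes, from the cohort | none |
| 6–59 months, enteropathy substudy | yes | matched within bands 6–11, 12–23 and 24–59 months |
| 6–59 months, cohort only | yes | same age range, not matched |

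**3. Size, for illustration.** The plan gives no figure for this contrast to reproduce.

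*From the article:* up to 200 SAM children and 200 controls (Sample sizes, Immunology substudy); estimated HIV prevalence 40% (Sample sizes, Observational study); 100 HIV-positive and 100 HIV-negative controls (Table 1).

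*Assumed:* share of cases under 6 months f = 10–20%; age shift in a marker d = 0.5–1 SD; no true SAM effect; two-sided 5% test; 40% HIV prevalence in the immunology cases, giving 0.40 × 200 = 80 HIV-SAM and 120 HIV-negative; the same f in both HIV groups.

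Spurious difference b = f × d:
- 0.10 × 0.5 = 0.05 SD
- 0.10 × 1 = 0.20 × 0.5 = 0.10 SD
- 0.20 × 1 = 0.20 SD

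Standard error = √(1/n₁ + 1/n₂) in SD units. False-positive rate = Φ(b/SE − 1.96) + Φ(−b/SE − 1.96).

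| Cases v controls | SE | b = 0.05 | b = 0.10 | b = 0.20 |
|---|---|---|---|---|
| Pooled, 200 v 200 | 0.100 | 7.9% | 17.0% | 51.6% |
| HIV-SAM, 80 v 200 | 0.132 | 6.7% | 11.8% | 32.7% |
| HIV-negative SAM, 120 v 200 | 0.115 | 7.2% | 13.9% | 41.0% |
| HIV-SAM, 80 v 100 of same HIV status | 0.150 | 6.3% | 10.2% | 26.6% |
| HIV-negative SAM, 120 v 100 of same HIV status | 0.135 | 6.6% | 11.4% | 31.5% |

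The planned comparison separates SAM by HIV status, so the lower four rows are closer to it. Their range is about 6–41%, against 8–52% pooled.

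**4. Precision after restriction to 6–59 months.** Minimum detectable difference at 80% power = (1.96 + 0.84) × √(1/n₁ + 1/n₂).
- Pooled: 0.280 SD with 200 v 200; 0.288 with 180 v 200 (10% removed); 0.297 with 160 v 200 (20% removed).
- Smallest split: 0.420 SD with 80 v 100; 0.448 with 64 v 100 (20% removed).

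**The case against.** The strongest case against accepts the eligibility facts and contests what follows from them.

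- **No evidence of an age effect or of many infants.** This stands. The article does not say that innate function differs before 6 months, nor how many infants qualify. A reader might infer that the comparison is shown to be biased; the article supports only that it is unprotected. The article does, however, treat age as relevant, since it bands controls by age and lists age among the confounders in the infection models.
- **The pooled error rate is not the planned test.** This stands. A reader might take 8–52% as the error rate of the plan, but the analysis separates SAM by HIV status, which lowers the range. The article also treats all analyses as exploratory and reads p values as strength of evidence. That weakens a false-positive rate as a measure of harm, but does not remove confounding.
- **Matching above 6 months belongs to the analysis plan.** This largely stands. Controls of the same age range exist, so an age term can deal with it, and an unseen plan may contain one. It cannot supply controls under 6 months.
- **Reused weights do not make ageing look like recovery.** This stands. A reader might infer that carrying baseline weights forward creates false recovery. Ageing accompanies follow-up whatever the weights, and the plan also models individual immune parameters that use none. The real limit is that controls are not followed, so maturation cannot be separated from recovery.
- **Keeping infants by projection and age adjustment would not work.** This stands. Within a child, age and follow-up time advance together, and hierarchical clustering gives no rule for assigning projected children.

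**Conclusion.** The point holds in a limited form. Immunology cases start at 0 months, controls start at 6 months, and the stated SAM-versus-control comparison has no age restriction. For SAM infants under 6 months, age and SAM cannot be separated in that contrast, and those infants also contribute to the baseline component weights.

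The mismatch is certain from the text; its size is not. The 0.05–0.20 SD spurious difference and the 6–41% (HIV-split) or 8–52% (pooled) error rates rest on an assumed infant share of 10–20%, an assumed shift of 0.5–1 SD and, for the split, 40% HIV prevalence among the cases. With few infants or no age effect the bias would be negligible.

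The point does not extend to the whole substudy. Analyses of infection and death within SAM do not use the controls as comparator.

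**What to change.** 1. Limit every SAM-versus-control immune comparison, and the derivation of the component weights used for it, to SAM children aged 6–59 months at sampling.
2. Include age in that comparison, because cohort-only children are not matched to the controls.
3. Report infants under 6 months separately in the within-SAM analyses. State that, without followed controls, their change over 48 weeks cannot be separated from maturation.

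**Cost.** This changes the analysis specification and needs no new recruitment. The case-control contrast loses the infants under 6 months, for whom it has no comparator, and a little precision: the pooled minimum detectable difference goes from 0.280 to about 0.29–0.30 SD if 10–20% of cases are removed. Profiles for the infants' within-SAM analyses need their own specification, since clusters derived at 6–59 months do not assign them.
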